# Use of cannabinoid-based medicine among older residential care recipients diagnosed with dementia: study protocol for a double-blind randomised crossover trial

**DOI:** 10.1186/s13063-020-4085-x

**Published:** 2020-02-14

**Keywords:** Dementia, Medicinal cannabis, Quality of life, Pain, Behavioural and neuropsychiatric symptoms of dementia (BPSD), Crossover trial

## Abstract

**Background:**

Dementia is a neurological condition that affects the cognitive and functional ability of the brain and is the leading cause of disability among those aged 65 years and above. More effective ways to manage dementia symptoms are needed because current treatment options (antidepressants and antipsychotics) can be ineffective and are associated with substantial side effects, including increased rate of mortality. Cannabinoid-based medicine (CBM) has shown an ability to inhibit some symptoms associated with dementia, and the adverse effects are often minimal; yet, little research has explored the use of CBM among this population.

**Aim:**

To monitor the safety of a purified dose of CBM oil (3:2 delta-9-tetrahydrocannabinol:cannabidiol) on behaviour symptoms, quality of life and discomfort caused by pain.

**Methods/design:**

We will carry out an 18-week, randomised, double-blind crossover trial that consists of a 2-week eligibility period, two 6-week treatment cycles, and two 2-week washout periods (between both cycles and after the second treatment cycle). We aim to recruit 50 participants with dementia who are living in residential aged-care facilities. The participants will be randomised into two groups and will receive a dose of either CBM oil or placebo for the first treatment cycle and the opposite medication for the second. Data will be collected using the Neuropsychiatric Inventory Questionnaire, the Cohen-Mansfield Agitation Inventory, the Quality of Life in Alzheimer’s Disease questionnaire, and the Abbey Pain Scale on seven occasions. These will be completed by the participants, aged-care staff, and nominated next of kin or family members. The participants’ heart rate and blood pressure will be monitored weekly, and their body composition and weight will be monitored fortnightly by a research nurse, to assess individual dose response and frailty. In addition, pre- and post-surveys will be administered to aged-care staff and family members to understand their perceptions of CBM and to inform proposed focus groups consisting of the aged-care staff and next of kin.

**Discussion:**

The study design has been informed by medical professionals and key stakeholders, including those working in the residential aged-care industry to ensure patient safety, collection of non-invasive measures, and methodological rigor and study feasibility.

**Trial registration:**

Australian New Zealand Clinical Trials Registry, ACTRN12619000474156. Registered on 21 March 2019

## Background

Dementia is a collection of symptoms that progressively reduces the cognitive and functional ability of the brain [1] and affects memory, intellect, rationality, social skills and physical functioning [2]. The symptoms associated with dementia present themselves in a variety of ways and can include depression, frustration, clinginess, forgetfulness, wandering, sexual aggression, hoarding, sleep disturbances and ‘the sundowner effect’ (increased manifestations of challenging behaviours at the end of the day [3]). Severe cognitive fluctuations in patients with dementia have been associated with an individual’s impaired ability to engage in activities of daily living, including social interactions and poorer quality of life (QOL) [4]. The slow progression and degeneration of dementia require that the affected individual receive additional support and assistance to remain at home or ultimately admission into residential aged-care facilities with 24-h care.

Dementia is the second leading burden of disability among Australians aged 65 years and older, and the burden of disease is expected to increase exponentially over the next 30 years [5]. Alzheimer’s disease is the most common cause of dementia and affects approximately 50–70% of the elderly with dementia. Pharmacological management of behavioural and physical symptoms of dementia is currently the most common treatment option, and many are prescribed medications such as off-label antipsychotics, sedative/hypnotics, anxiolytics, acetylcholinesterase inhibitors, and antidepressants to mask and alleviate the array of dementia symptoms [6, 7]. Medications such as aripiprazole, olanzapine, risperidone and memantine have been shown to reduce troublesome behaviours [8], although unclear guidelines are often provided for administration [2, 7]. This results in polypharmacy and its inherent risks, with numerous medications being prescribed for a longer duration than recommended [9]. Many of these medications lead to a number of substantial side effects [10], including increased rate of stroke and mortality [11].

Cannabinoid-based medicines (CBMs) have been shown to improve dementia symptoms such as aggression and agitation [12, 13], and they appear to be safer to prescribe than other pharmacotherapies [3] because the adverse effects are often minimal [14]. For example, Weier and Hall [15] found sedation to be the only adverse effect among patients with dementia prescribed either cannabinoids or pharmacotherapies. While periods of euphoria, somnolence and tiredness were observed among those prescribed dronabinol, a synthetically derived delta-9-tetrahydrocannabinol (THC) [16], there were only a small number of adverse events (6 of 98) related to the administration of the synthetic THC similar to those manifested by the placebo [14, 17]. However, well-designed, randomised, double-blind, placebo-controlled trials need to be completed to understand the most efficacious formulation, safety profile, drug–drug interactions and true effect to determine the place of CBM in dementia [18, 19], allowing greater generalisability of these outcomes [20].

A range of CBMs (synthetic compounds such as dronabinol or nabilone or pure cannabinols) are available; however, the combination of cannabidiol (CBD; the non-psychoactive compound) and THC (the psychoactive compound) [21] appear to be most effective, because both compounds improve psychomotor activity, mood, sleep–wake cycles and eating behaviours [14, 22, 23]. THC and CBD interact with the endogenous cannabinoid systems CB1 and CB2 receptors [19, 23, 24], producing symbiotic neuroprotective effects. For example, in pre-clinical trials, THC is found to be a partial CB1 antagonist and improves immune function [25], encourages amyloidogenesis [14, 22, 23, 26, 27], reduces neuropsychiatric symptoms, reduces pain sensation [28], stimulates appetite [21–23, 29], and inhibits acetylcholinesterase, similarly to cholinesterase inhibitors such as donepezil [30]. CBD is an inverse CB1 agonist [31] that promotes neurogenesis and vasodilation within the brain; increases neuronal plasticity and cerebral blood flow [32]; prevents cell destruction; and has anti-inflammatory (neuroinflammation and peripheral inflammation), analgesic, anticonvulsant and anxiolytic properties [25]. CBD is an important compound because it reverses the negative cognitive consequences and ameliorates the psychoactive properties of THC [21–23, 29].

Studies assessing the safety and efficiency of CBMs have shown many benefits among other neurodegenerative diseases, such as Parkinson’s disease [33, 34], epilepsy, post-traumatic stress disorder [18, 35], anxiety [12], and spasticity due to multiple sclerosis [36], with the use of CBM reducing benzodiazepine prescriptions by 45% [37]. However, only a handful of studies have investigated the use of CBM in patients with dementia [13, 14, 23]. Recently, an observational study monitored the use of a CBM medication over a 2-month period among ten females with severe dementia and found a 40% reduction in behavioural problems and 50% reduction in rigidity [38].

The pharmacodynamics and pharmacokinetics of THC (weeks 1–6, 0.75 mg; weeks 7–12, 1.5 mg) administered to ten participants with dementia was safe and well tolerated [14]. Administration of THC 2.5 mg in 11 patients with dementia demonstrated positive effects on mental state; dementia severity; and behavioural symptoms such as delusions, irritability, sleep and caregiver distress [23]. Studies reporting the use of dronabinol (2.5 mg daily) found improvements in anorexia and body weight, as well as less disturbed behaviours [16] such as agitation and motor behaviours, with no adverse effects observed [39]. Retrospective observations of dronabinol administration among 40 hospitalised patients indicated improvements in agitation and aggression, sleep duration, and meal consumption [13]. Two independent case studies monitoring the effects of nabilone (maximum dose 0.5 mg twice daily for 6 weeks) among elders with dementia found improvements in severe agitation and aggression [40], psychomotor activity, and smiling, as well as positive experiences among family members [41]. No changes in the number of falls or in balance (with eyes open) were reported among 18 participants administered 1.5 mg of oral THC twice daily [42], with recommendations suggesting higher doses (THC 1.5 mg three times daily), and longer study durations (great than 3 weeks) are needed to understand the true effects on behavioural symptoms, including QOL and activities of daily living [43]. Therefore, further research in this area is needed because many beneficial outcomes have been reported, although dosing, samples size, patient cohort (2–50 participants) and outcomes have varied in what are generally small studies with poor experimental designs.

### Aims

The primary aim of the present study will be to see if a purified CBM oil is safe and improves behavioural and neuropsychiatric symptoms of dementia (BPSD). In addition, two secondary aims of this study will include examining QOL and discomfort caused by pain among patients with dementia receiving CBM oil.

## Methods and general study design

This study has received approval from the Human Ethics Research Committee at the University of Notre Dame Australia. The study will use a parallel mixed methods design. The research methodology for this study is a phase II, randomised, placebo-controlled crossover trial. The design will include a 2-week eligibility (assessment) period, two 6-week-treatment cycles to allow each participant to take part in both the control and treatment cycles, and two 2-week washout periods (one between both treatment cycles and the other after the second treatment cycle). The 6-week treatment cycles have been selected on the basis of safety, pharmacodynamics, and pharmacokinetics as reported by Ahmed et al. [14], and a 2-week washout period has been shown to be safe and an appropriate length of time for cannabis to metabolise in older individuals [44].

In addition, residential aged-care staff and next of kin perceptions towards the use of CBM oil will be evaluated via surveys administered prior to and upon completion of the study. At the end of the second treatment cycle, the residential aged-care staff and family members will be asked to participate in a follow-up focus group to gather more in-depth information regarding individuals’ perceptions before and after the administration of CBM. Each participant will be in the trial for approximately 4 months (18 weeks), but the duration of the study will last over 12 months in order to recruit participants from a number of aged-care facilities.

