### Rigor

Residential aged-care staff usually work within the aged-care setting for at least 3 months and therefore are likely to be working in the same facility for the duration of the 4-month trial. The same aged-care staff member will monitor the same participant(s) for the duration of the study and report any changes on the participants’ behalf. To be classified as a residential care staff member, the individual must spend at least two occasions per week with the participant. The same registered nurse will administer the medication for both treatment cycles.

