### Data collection

The aged-care staff, resident participants with dementia, and nominated next of kin will complete a total of four outcome measures on seven occasions throughout the study. The questionnaires take approximately 20 min to complete and will be completed three times during the first treatment arm (baseline [day 0], after maximum tolerated dose has been reached [day 24], and the end of the treatment cycle [day 42]), three times during the second treatment arm (baseline [day 56], after maximum tolerated dose has been reached [day 80], and the end of the treatment cycle [day 97]) and once following the 2-week washout period after the second treatment arm (day 112). The questionnaires will be administered by the primary researcher.

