### Process evaluation outcomes

The one-page pre- and post-surveys will be administered to aged-care staff and next of kin at the beginning of the first treatment cycle and at the end of the second treatment cycle. These surveys comprise seven to nine questions regarding individuals’ perceptions towards CBM oil use and the symptoms of dementia they find most challenging. A total of six questions will be asked during the focus group discussions. These questions relate to positive and negative observations among those taking CBM oil, as well as changes in perceptions, knowledge and benefits regarding the use of CBM use.

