### Data analysis

#### Quantitative

The results of questionnaires completed on behalf of the aged-care staff, participants and family members will be analysed using IBM SPSS Statistics version 25 software (IBM, Armonk, NY, USA). The responses from the aged-care staff will be the main responses considered for analysis. Where available, participants and family responses will be included for secondary analysis. To examine group differences, the participants will be categorised according to their treatment cycle group allocation (group A or group B). Descriptive statistics will be derived. Each variable will be tested for normality. For those variables that meet the normality assumption, two-sided paired and/or independent *t* tests will be used to examine group differences within and between groups. If the normality assumption is violated, then non-parametric tests such as the Wilcoxon signed-rank test will be used. Within-subject differences of the four measurements between the first and second washout periods will be tested using paired *t* tests to ensure that the washout phase is long enough to rule out any carryover effects [51, 52]. All data collection points will be examined using general linear mixed modelling techniques to see if any changes in behaviour, QOL or pain have occurred over the duration of both treatment cycles. The covariates of weight, average dose of medication, and baseline measures will be controlled for in each model, and any interactions will be tested and reported. The proportion of adverse events during the CBM and placebo phases will be tested and reported for each individual. NPI-NH is the primary outcome measure for this study. All other measures (CMAI, QOL-AD, and Abbey Pain Scale) have been included for secondary analysis. The CMAI will be analysed using the reliability change methodology compared with the NPI-NH to allow small changes to be reported [53]. The α-value will be set at 0.05. In the instance where a participant withdraws halfway through a treatment cycle, the information collected prior to withdrawal will be retained in the study because their personal information will have been de-identified. The data management of the information collected will follow standard university procedures, be stored in a locked cabinet for a period of 15 years, be stored on a password-protected computer, and be backed up regularly in a secure format.

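### Post-survey and focus-group invitation reach the outcome raters at the end of cycle 2, before their day-112 ratings, and the two statements of survey timing conflict

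*Protocol article*

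**What the plan says.** **Timing of the survey and focus group.** Methods and general study design says that staff and next-of-kin perceptions "will be evaluated via surveys administered prior to and upon completion of the study". The next sentence dates the focus-group request: "At the end of the second treatment cycle, the residential aged-care staff and family members will be asked to participate". Process evaluation outcomes dates the surveys differently: "at the beginning of the first treatment cycle and at the end of the second treatment cycle".

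**Content.** Process evaluation outcomes says of the focus-group questions: "These questions relate to positive and negative observations among those taking CBM oil". The one-page survey covers views of CBM oil and the symptoms that respondents find hardest to deal with.

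**Ratings.** Under Data collection, staff, residents and next of kin complete the outcome measures seven times. The sixth occasion is "the end of the treatment cycle [day 97" and the seventh is "once following the 2-week washout period after the second treatment arm (day 112". Data analysis, Quantitative, adds: "The responses from the aged-care staff will be the main responses considered for analysis". Rigor says: "The same aged-care staff member will monitor the same participant(s) for the duration of the study".

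**Blinding.** Only the laboratory manager knows the allocation, and it is released after the study is complete.

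**The concern.** The NPI-NH is a subjective primary outcome, and the staff who rate it also supply the process evaluation. Every resident receives both treatments in an order that staff do not know. A staff member asked what was seen in residents on CBM oil can answer for a particular resident only by guessing which cycle was active. A group discussion pools those guesses. If this happens before the person's ratings are finished, the later ratings may reflect the guess as well as the resident.

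Two sets of ratings could be touched. One is the same resident's day-112 rating. The other is the ratings of any other resident whom that person still follows. Nothing in the article requires a rater to finish rating before taking the survey or joining a group.

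**Working it through.** **1. The schedule's own days.** Cycle 1 runs from day 0 to day 42. Adding the 14-day washout gives 42 + 14 = 56, the stated baseline of cycle 2. Adding six weeks gives 56 + 42 = 98, where Data collection states day 97. Adding the second washout gives 98 + 14 = 112, the stated last rating, which is also 16 weeks × 7 days.

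**2. Gap between the survey or invitation and the last rating.** From the stated day, 112 − 97 = 15 days. From the derived day, 112 − 98 = 14 days. Either way it is about two weeks.

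**3. The two survey dates side by side.**

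| Section | Post-survey | Relative to day 112 |
|---|---|---|
| Methods and general study design | study completion | after, on a natural reading |
| Process evaluation outcomes | end of cycle 2 | 14 to 15 days before |

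Both cannot hold. The focus-group invitation is dated to the end of cycle 2. The date of the session itself is not given.

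**4. Which of a resident's own ratings are exposed.** The ratings on days 0, 24, 42, 56, 80 and 97 come before the end-of-cycle-2 survey or fall due with it. Only day 112 comes after: 1 of 7. It is used twice in Data analysis, Quantitative. First, it is the second-washout value in the paired comparison of the two washouts that serves as the carryover check; the first-washout value (day 56) comes before the survey, so only one side of that comparison is exposed. Second, it is one of the time points in the mixed model.

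**5. Whether residents can overlap.** Trial status puts recruitment from February 2020 to about 20 July 2020. Assuming a start between 1 and 29 February, the window is 142 to 170 days, longer than the 97 days to the end of cycle 2. Early residents can therefore reach that point while later ones are in treatment. Rigor allows one staff member several residents but gives no number per rater and no spacing between their starts.

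**6. What would follow if a rater were shared.** Suppose a second resident starts *d* days after the first. When the first reaches day 97, the second is on day 97 − *d*.

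- For *d* = 1 to 54, the second resident's day-42 rating is already in, and of the two end-of-cycle ratings only day 97 is to come.
- For *d* = 55, the day-42 rating is due that same day.
- For *d* = 56 to 97, both end-of-cycle ratings are to come.

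The documents do not give *d*, so they do not determine how much of the treatment contrast would be exposed.

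**7. Sample size.** The target of 40, raised to 50 for attrition, plays no part in this and does not change.

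**The case against.** **Only the invitation is dated.** Six groups of six to eight people are planned for the whole trial, so the groups must pool people across residents and cannot follow each resident's own end of cycle 2. Later sessions fit this at least as well. A condensed article may also leave session dates to the full protocol. This stands: it cannot be said that the focus groups precede day 112. But the survey's date is given twice and inconsistently, and one of those dates falls before the last rating.

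**Blinding is not broken.** A reader might infer that these activities unblind the raters. They do not, because nobody at the facility holds the allocation. The survey is a short individual form with no sharing described. What remains is a risk that raters form beliefs, and pool them where groups meet.

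**Overlap within one rater is inferred.** A reader might take it that staff will be discussing CBM while other residents they rate are on treatment. The article attributes the long study duration to recruiting from several facilities, which is compatible with enrolling one facility at a time. The overlap is possible and plausible, not stated.

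**Bias in the treatment contrast is not shown.** A reader might infer a biased treatment effect. A general shift in a rater's outlook that affects both of a resident's periods tends to cancel within the resident. Bias needs guesses that track the true order, and discussing one resident does not reveal another's order. This also stands.

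**Beliefs form anyway.** Staff record adverse events during titration and pass them on at shift changes. The added effect of the survey or group is therefore unknown. It is still avoidable, since only its timing creates it.

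**Conclusion.** The point holds in a limited form. On the timing in Process evaluation outcomes, the post-survey reaches the outcome raters about two weeks before their last rating. The focus-group invitation is issued at the same point, and no rule puts the ratings first. The two statements of survey timing contradict each other.

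The exposure that follows from this timing is the day-112 rating, one of seven per resident, in the carryover check and the mixed model. For the survey this rests on the end-of-cycle-2 date being the one applied; for the focus groups, on sessions being held before day 112. A resident's own ratings from day 0 to day 97 are not affected by that resident's end-of-cycle-2 survey, assuming that the day-97 rating is completed before the survey handed out at the same time. Ratings of residents still on treatment are at risk only if one rater follows residents with staggered starts.

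The documents give no basis for a size or direction of bias. This is an avoidable risk to subjective ratings and does not show that the primary comparison is compromised.

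**What to change.** Reconcile the survey timing in Methods and general study design with that in Process evaluation outcomes. State in both places that, at each facility, post-surveys and focus groups are held only after the last participant there has completed the day-112 assessment. The focus-group invitation can move with them.

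This changes timing only. Sample size, visit schedule and outcome measures stay as they are. The cost is longer recall for staff and families of early participants, in a component that the article itself describes as exploratory.
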